### Logic model

To plan the evaluation, a logic model has been developed. The model is based on the assumption that regular physical activity has a positive impact on health for those who were inactive. [19]. This long-term outcome is shown on the right-hand side of Fig. 1. In the second column from the right, we indicate the expected interim goal of the programme, i.e. participants of the intervention group who received the starter package visit the regional standardised exercise programmes after they return home. The key mechanisms (or psychological mediators) that if enhanced are likely to lead to increased attendance of the exercise programmes are shown in the second column from the left. Finally, in the far left column of Fig. 1, the activities which will take place during the residential stay are listed.

**Fig. 1 Fig1:**
[figure not shown]
Logic model of the study

### Measurements

All study participants will be evaluated at two or three points in time (see Table 2).

**Table 2 Tab2:** Time schedule for the different measurements

	Baseline	Baseline fitness^a^	Follow up1^b^	Follow up2^c^
	PA & mediators		PA & mediators	PA & mediators and fitness
Physical activity (accelerometer, log book)	✓		✓	✓
Questionnaire	✓		✓	✓
Anthropometry		✓		✓
Cardiovascular fitness (bicycle ergometer test)		✓		✓
Physical function (6MWT, handgrip, balance)		✓		✓
Blood chemistry – laboratory		✓		✓
Medication		✓		✓

^a^directly after the stay at a health resort

^b^= 10 weeks after the beginning of the stay in the health resort

^c^= 12 months after the beginning of the stay in the health resort

Physical activity will be objectively measured using an accelerometer (GENEActiv) together with a physical activity log book before the residential stay (T1), 10 weeks after the first day at the health resort (T2) and 12 months after the first day at the heath resort (T3). Participants will be instructed to wear the accelerometer during seven complete and consecutive days, 24 h each day. At the same time, a log book should be filled in detailing walking and cycling for transport, walking and cycling during leisure time and strength training. At the same time points, participants will be asked to fill in the Office in Motion Questionnaire [20].All study participants (from the intervention and the control groups) will be encouraged to participate in an ergometer test, three functional fitness tests and some laboratory tests. Cardiovascular fitness will be tested with a bicycle ergometer to exhaustion [21, 22]. In general, subjects should reach maximum exercise capacity in 8 to 12 min [23]. To ensure that the ergometer test protocols can be compared, all participants will have to perform the same test protocol, which consists of a 35-watt initial loading increment for 2 min. Subsequently, the work load will be increased by 10 watts every minute. Work capacity will be measured in watts. Maximum heart rate and Borg-RPE will be documented as parameters for exhaustion [24].Physical function will be evaluated with the 6-Minute Walk Test [25]. Participants will be encouraged to walk a maximum possible distance within 6 min, during which modifying the speed will be tolerated. Muscle strength will be measured using a handgrip dynamometer (Jamar hydraulic hand dynamometer J00105) [26] and balance will be tested using the one-leg stand [27].Quality of life will be assessed by the World Health Organisation Quality of Life WHOQOL-BREF scale [28]. Psychological mediators such as motivation [29], satisfaction with life [30], satisfaction with the built environment [5], positive and negative effects [31], self-efficacy [32], social support [33] and enjoyment of physical activity (single item) will be determined via questionnaire. Country of birth and education level will also be recorded.As anthropometric measurements, body weight, body height and abdominal girth will be evaluated.Laboratory parameters, including glucose, high density lipoprotein, low density lipoprotein, triglyceride, creatinine, sodium, potassium, calcium, chloride, phosphate, bicarbonate, GGT, GOT, GPT, BNP, NT-proBNP and HbA1c, will be recorded, and medication will be derived from the patient’s chart.

### Process evaluation: patient flow

We will analyse how many of the potential participants are willing to take part in the physical activity measurements (accelerometer together with the log book) prior to the residential stay. After that, the number of people who start the exercise programme will be evaluated, as well as the reasons for continuing the programme or quitting it after the 12 free sessions. The number of attended sessions will also be evaluated. Patient flow is shown in Fig. 2.

**Fig. 2 Fig2:**
[figure not shown]
Flow chart of the study

Within this project, the implementation of an interface function at the health resorts will be tested. Therefore, the focus will be on the processes during the residential stay, which should lead to participation in the regional exercise programmes. The key outcome will be the number/percentage of people who are informed at the health resorts and are finally allocated to the regional exercise programmes. The counterpart to the interface function in the health resorts will be the regional, standardised, sports club based exercise programmes. The process evaluation will be aimed at determining the factors that are necessary to implement new community-based health-oriented physical activity programmes. The process evaluation is summarized in Table 3.

**Table 3 Tab3:** Process evaluation: questions and measures

Task	Process evaluation	Measures
Willingness for physical activity measurement	How many potential participants return the form?	Number of people who return the form
	How many are willing to participate in the activity measurement?	Number of people who are willing to participate in the activity measurement
Information and recruitment during the residential stay	How many persons are generally informed?	Number of informed people
	Which materials are used?	Number of people who arrange a start date for the initial exercise programme
	On which occasion is the regional programme presented?	
	Percentage of people for whom a start time of the regional programme has been scheduled	
Initial exercise programme	How many people actually start the regional programme?	Number of people who start the initial exercise programme
	Reasons for sustainable participation or for drop-out	Number of successful participants
Long-term exercise programme	How many people continue with the long-term programme?	Number of people who start the long-term exercise programme
	Reasons for sustainable participation or for drop-out	Number of successful participants

### Statistical analyses

All the statistical analyses will be performed with IBM® SPSS® Statistics for Windows, Version 20 (IBM Corp., Armonk, NY, U.S.). P-values <0.05 will be considered to be statistically significant, and all tests will be two-sided. Data exploration using descriptive statistical analysis and inferential statistics will be performed. The sample data will be carried out by frequencies or percentages (categorical variables), means and standard deviations (continuous variables) and graphics. T-tests and chi-square tests will be used to compare the groups. If a normal distribution is not met, non-parametric tests will be applied. Analysis of covariance (ANCOVA) (comparing parameters after the intervention and after the follow-ups) between the intervention and control groups will be adjusted for the baseline values as the covariate analysis is performed.

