## Methods/Design

### Overview

The proposed study is designed as a prospective, controlled, multicentric open-label study that will take place in the federal state of Styria, Austria. Austrian health resorts (*n* = 149) who accommodate patients from Styria will be involved. Based on the communities people come from, the study participants will be divided into an intervention group and a control group. Eight different communities in the federal state of Styria have been selected. Four communities will provide regional, standardised, sports club based exercise programmes and four matched communities will not offer these programmes in the near future. In short, the process will be as follows. People from the eight communities will be approached before the residential stay and asked whether they agree to fill in a questionnaire and participate in a seven-day physical activity measurement programme. Those who agree and do not meet the WHO physical activity guidelines will be included in the study [3]. During the residential stay, members of the intervention group will receive information about the regional, standardised, sports club based exercise programmes in their close living environment. Members of the control group will receive a brochure about physical activity.

The study was approved by the local ethical committee (University of Graz, EK-NR 86-2014/15) and will be conducted according to the principles of the Declaration of Helsinki. Furthermore, the protocol was registered at ClinicalTrials.gov (identifier: NCT02552134).

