In detail: four Styrian communities were selected according to the postal code as intervention regions because they have well-developed sports club networks. In these urban and rural communities, regional, standardised, sports club based exercise programmes will be provided twice a week. Because the number of inhabitants of three of the communities is relatively small, we decided to selected similar communities as controls and not to randomly select people of the same area for the intervention and control groups. The controls live in four different regions that are similar with regard to size, urban or rural alignment and sports club networks. As soon as the inhabitants of the eight communities have received approval from their health insurance companies for the residential stay in a health resort, they will be contacted and asked whether they agree to the measurement of their physical activity behaviour before the residential stay, and they will also be asked to fill in a questionnaire. If they are willing to take part in the activity analysis, they will have to return a form giving consent to the procedure and providing the assumed start day of the residential stay. Those who do not meet the WHO physical activity guidelines will be eligible for the study and will be asked during their residential stay whether they agree to participate in the study.

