### Intervention

During the residential stay in the health resort, members of the intervention group who do not meet the physical activity guidelines based on the accelerometer data will receive a so-called “starter package”. During the stay at the health resort, people who took part in the prior physical activity measurement programme will be informed about the regional programmes if they do not meet the physical activity guidelines.

This starter package will include information about the project, an informed consent form, as well as a voucher for 12 regional, standardised, sports club based exercise sessions which can be attended immediately after the stay. The costs for these 12 sessions will be covered by the project funds so that participants need not pay any fee. Ideally, the beginning of the regional, standardised, exercise programme should be scheduled during the residential stay. “Standardised” means that the instructors will receive an obligatory 18-h training programme, and the sessions will have a defined structure with the following quality criteria [14]:Number of exercise sessions per week: two sessions.Duration of each single session: 90 min.Maximum number of people in a training group: 12 people.Cardiovascular exercise during a single session: ≥40 min of moderate- to vigorous-intensity aerobic activities.Muscle-strengthening activities during one session: ≥30 min; ≥2 sets of ≥6 different muscle-strengthening activities.Coordination and flexibility: will not be performed as a distinct part but it will be integrated in the cardiovascular and muscle-strengthening sections of the programme.Feedback on individual physical activity goals: as a supplement to the standardised exercise programme, individual “physical activity homework” will be prescribed to ensure that the physical activity recommendations can be realised. Furthermore, participants will be encouraged to support each other by identifying helpful behaviour change strategies and applying social support. Ten minutes will be reserved for this at the beginning and end of each session.

The advanced job training will include lectures and a manual with 12 different predefined sessions. Furthermore, health aspects of physical activity will be introduced, as well as extended communications training.

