### Sample size calculation

For the sample size calculation, the difference in minutes of MVPA measured in bouts ≥10 min is considered as a suitable parameter for health-enhancing physical activity [16]. According to several studies, MVPA is an appropriate parameter for that purpose [17, 18]. Jung et al. [16] evaluated the changes in MVPA after a supervised exercise intervention in a similar cohort (male and females, aged 51(10)) years suffering from prediabetes). After the intervention, MVPA was changed by 44.5 (72.2) minutes. Due to the fact that the intervention-induced changes in our study are supposed to be similar, we considered the changes in MVPA of the above-mentioned study to calculate the sample size in our study.

Given a clinically relevant difference of 44.5 min of MVPA between the intervention and control groups, a standard deviation of 72.2 MVPA of the differences and a two-sided significance level of 0.05, a sample size of *n* = 42 per group is needed to reach a statistical power of 80 %. Since drop-outs and those lost to follow-up may have an inestimable effect on the assumed standard deviation of the differences, the sample size will be increased to *n* = 48 persons per group. Expected value μ1 (intervention) = 84.1 MVPA, μ2 (control) = 39.6 MVPA. Calculations were undertaken via: http://www.clinical-trials.de/de/Werkzeuge/werkzeuge.html

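### Four communities are compared with four, but the sample size and the planned tests treat participants as independent: any positive between-community correlation takes the error above 5%, and 42–48 per group does not give 80% power on 6 df

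*Protocol article*

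**What the plan says.** **Allocation.** The Overview says: "Based on the communities people come from, the study participants will be divided into an intervention group and a control group". It continues: "Four communities will provide regional, standardised, sports club based exercise programmes and four matched communities will not offer these programmes in the near future". Eligibility and recruitment explains that three of the communities are small, so "we decided to selected similar communities as controls and not to randomly select people of the same area for the intervention and control groups". No community supplies people to both arms.

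**Delivery.** In the intervention arm the sessions are run by regional clubs in groups. One quality criterion in the Intervention section reads: "Maximum number of people in a training group: 12 people".

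**Sample size.** The Sample size calculation starts: "Given a clinically relevant difference of 44.5 min of MVPA between the intervention and control groups". It adds a standard deviation of 72.2 and a two-sided level of 0.05, arrives at 42 per group for 80% power, and raises this to 48 on account of drop-out and loss to follow-up. No ICC, design effect or number of communities enters. Eligibility and recruitment gives a total of 194 participants.

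**Analysis.** Statistical analyses states: "T-tests and chi-square tests will be used to compare the groups". Non-parametric tests replace these if normality fails, and an ANCOVA adjusts the between-arm comparison for the baseline value. The section names no community effect, cluster summary or robust variance, and makes no use of the matching.

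**The concern.** When whole communities form the arms, the arm difference is a difference between two sets of four community averages. Anything that moves a community's average (its clubs, its instructors, its training groups) is part of the noise in that difference. Adding participants within the same communities does not average it away.

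Tests that count each participant as a separate, independent observation leave this noise out of the standard error. The reference distribution is wrong as well: eight communities support about 8 − 2 = 6 degrees of freedom for the arm contrast, whereas an individual-level test on 42 per group uses 82.

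Two things are at stake for the primary outcome, weekly MVPA. A chance difference among eight communities could be reported as a programme effect, and the stated 80% power may not describe what a test suited to this allocation would achieve.

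**Working it through.** **Inputs from the protocol article.** Difference d = 44.5, SD s = 72.2, two-sided α = 0.05, power 80%, 42 per group raised to 48 (Sample size calculation); 4 + 4 communities (Overview); 194 participants (Eligibility and recruitment), which is 97 per arm if split equally.

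**Assumed.** ICC of 0.01, 0.02 and 0.05, with 0 as the reference case; equal community sizes.

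**1. The plan's own figure.** For independent individuals,

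n = 2 (1.960 + 0.842)² × 72.2² / 44.5² = 41.3, rounded up to 42 per group.

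Power at 42 is 80.6% by this normal formula; the exact t-test gives 79.7% at 42 and asks for 43. The published 42 is thus reproduced with no allowance for clustering.

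**2. Design effect.** DE = 1 + (m − 1) × ICC, where m = participants per arm / 4.

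- 48 per arm: m = 12, DE = 1.11 / 1.22 / 1.55
- 97 per arm: m = 24.25, DE = 1.23 / 1.47 / 2.16

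**3. Type I error of an unadjusted individual-level test.** Its standard error is too small by a factor of √DE, so the true error is 2 × [1 − Φ(1.96 / √DE)].

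| ICC (assumed) | 48 per arm | 97 per arm |
|---|---|---|
| 0 | 5.0% | 5.0% |
| 0.01 | 6.3% | 7.8% |
| 0.02 | 7.6% | 10.5% |
| 0.05 | 11.5% | 18.3% |

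Simulation (40,000 runs per setting) gave 6.2%, 7.6% and 11.3% with 12 per community, and 7.7%, 10.5% and 18.3% with 24. Unequal sizes make it worse: with 24, 8, 8 and 8 people in the four communities of each arm and ICC 0.05, the simulated error was 13.8%.

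**4. Power of a community-level test on 6 df.** Non-centrality λ = d / [s × √(2 × DE / n)], critical value 2.447, non-central t with 6 df. Example at n = 48 and ICC 0.02: λ = 44.5 / [72.2 × √(2 × 1.22 / 48)] = 2.73, power 63%.

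| ICC (assumed) | 42 per arm | 48 per arm | 84 per arm | 97 per arm |
|---|---|---|---|---|
| 0 | 66% | 71% | 91% | 94% |
| 0.01 | 62% | 67% | 86% | 89% |
| 0.02 | 58% | 63% | 80% | 84% |
| 0.05 | 50% | 53% | 66% | 68% |

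The 84 column is 21 completers per community. It applies to 97 the proportion implied by the step from 48 to 42 (42/48 = 0.875; 97 × 0.875 ≈ 85, or about 21 per community). At 97 per arm without losses, power is 80.5% at ICC 0.026 and 79.9% at 0.027, so 80% is lost just above 0.026. With 21 completers per community it is lost just above 0.02.

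**5. Participants needed for 80% with 4 + 4 communities on 6 df.** About 70, 84 and 224 per arm for ICC 0.01, 0.02 and 0.05. At ICC 0.10 no number suffices: as n grows, λ tends to 44.5 / [72.2 × √(2 × 0.10 / 4)] = 2.76, which corresponds to about 63% power.

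**The case against.** **The detail may sit in an unseen analysis plan.** This would answer a silence. Here the article states both a calculation and a set of tests, and both assume independent participants under an allocation that it describes as being by community. The objection fails.

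**The inflation is not shown to exist.** It requires an ICC above zero, and the document gives none. That stands: the error rates are conditional, and at ICC 0.01 with 12 per community the excess is modest. A reader might infer that the error rate is known to exceed 5%; the document supports only that it does so for any positive ICC.

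**The figures concern the unadjusted test.** The planned ANCOVA adjusts for baseline, which can absorb stable community differences and lower the relevant ICC. This stands as a limit on the sizes. Community, instructor or training-group effects that arise after baseline remain. The group effects apply only to those in the intervention arm who attend.

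**Power could still be adequate.** A reader might infer that no valid analysis of this design can reach 80%. The document does not support that: with the 194 participants of Eligibility and recruitment, the 6-df test reaches 80% for small ICCs. The shortfall is established only for the 42–48 per group on which the 80% is claimed. There, part of it comes from the few degrees of freedom: at ICC 0.01 and 48 per arm, a normal critical value would give 82%.

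**Six degrees of freedom is one choice.** If the matching is pairwise, a paired comparison has 3. The article does not say how the matching was done, so 6 is a working assumption.

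Shared terrain or weather might also be suggested as a cause of correlation. The article mentions neither, and each person is measured relative to their own stay, so the point does not rely on them.

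**Conclusion.** The concern holds with its conditions attached. The unit of allocation is the community, while the sample size and the tests use the individual.

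- **Error rate.** Above 5% for any positive ICC. Under ICC 0.01 to 0.05, equal community sizes and no baseline adjustment, it is about 6% to 12% at 48 per arm and 8% to 18% at 97 per arm.
- **Power.** At 42–48 per group a community-level test on 6 df misses 80% throughout, including at ICC 0. If 194 people are enrolled, 80% is kept up to an ICC of about 0.026 without losses, or about 0.02 with 21 completers per community.
- **Open conflict.** The totals of 194 and 2 × 48 = 96 cannot both be the basis of the power statement, and enrolling more people in the same eight communities raises the error of the planned tests.

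Because this touches the between-arm comparison of the primary outcome and the remedy is cheap, it should be corrected before analysis.

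**What to change.** 1. In Statistical analyses, make community the unit that the primary between-arm comparison respects. Either use a linear mixed ANCOVA with a random intercept for community and small-sample degrees of freedom (for example Satterthwaite), or compare baseline-adjusted community means on 6 df. Use a paired version if the matching is pairwise, and say whether it is. Report the ICC.
2. Reconcile the 194 participants in Eligibility and recruitment with the 96 implied by the Sample size calculation.
3. Then replace the 80% figure by the power under 4 + 4 communities, with expected losses, over a stated ICC range.

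**Cost.** Changed analysis wording, probably a wider confidence interval, and a less favourable power figure. No new data are needed to correct the standard error and the stated power. The change does not bring 48 per arm back to 80%; on the assumptions above that takes about 70 per arm at ICC 0.01 and 84 at 0.02. Nor does it remove confounding: the communities were chosen, the intervention ones for their developed club networks, and this limitation should be stated beside the result.

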## Discussion

This study is aimed at evaluating the effects and processes of regional, standardised, sports club based exercise programmes, which are promoted during a residential stay at health resorts. Thus, the health sector and the sports sector need to be linked. While the health sector informs and recruits the participants, the sports sector provides the regional, standardised, exercise programmes. In many European countries, widespread networks of sports clubs exist, but they are hardly ever used for standardised health-enhancing exercise programmes. In Germany, for instance, more than 91,000 sports clubs are registered, and 29.7 % of them provide general leisure time oriented programmes [34]. These programmes primarily focus on target groups that are already somewhat active [35]. Only 4.4 % of all German sports clubs provide exercise programmes that are financially supported by health insurance companies. In England and Scotland, studies have investigated professional football clubs as settings to provide prevention programmes [36, 37]. Although these programmes have showed great effects, they might not be easily transferable to other countries. In Great Britain, football is a kind of religion, and being on the same playing fields as the professional players was extremely important for the participants [38]. Certainly, in many other countries, football does not have the same importance. Similar to the studies in Great Britain, sports clubs as a non-clinical setting have also been used in an Austrian feasibility study [10]. However, differing from this feasibility study, no bicycle ergometers for cardiovascular exercise or multi-towers for resistance training were used in the regional, standardised, exercise programme. To ensure health effects, it is important to realise regular aerobic physical activity with a moderate or vigorous intensity, as well as muscle-strengthening activities [1]. The manual with the predefined exercise sessions will help to provide diverse aerobic exercises, as well as strength training, and is in line with the different guidelines describing the access to regional structures which provide exercise programmes as an important task in physical activity promotion [8, 39].

A major strength of the study will be the fact that different sectors will be cooperating and that physical activity will be measured objectively. Another strength will the process evaluation with the objective to learn about the implementation of exercise referral in medical settings. The study intervention itself will be another strength: the regional, standardised, exercise programmes have been developed by scientists, together with representatives of sports clubs. If the study participants attend the exercise programmes twice a week, they will almost meet the WHO physical activity recommendations.

A limitation of the study might be the recruitment that will be undertaken during the stay at the health resorts. Although the procedure is described in detail, it will be undertaken by employees of the resorts, and not by the study stuff. This is an important issue, because taking sustainability into account, it is the staff in the health resorts who should encourage people to attend regional, standardised, exercise programmes after their stay at health resorts in the future. Therefore, one of the most important questions in the process evaluation is how the staff in the health resorts succeed in recruiting participants for the regional programmes. A well-known barrier for the health professionals working in the resorts is that they are confronted with numerous patients, and that only a small number of them live in communities where regional exercise programmes are provided. As was found in other lifestyle programmes, the number of drop-outs or those lost to follow-up might be a limiting factor [40]. Due to the fact that the measurement of physical activity and its feedback in the preliminary studies was found to be appealing for the study participants, the number of drop-outs will hopefully be small. One factor which may be a slight limitation to the study is that people who quit the regional exercise programme or even never start it could also reach the weekly physical activity recommendation by being physically active independent of the regional exercise programme. Data from the questionnaire and information from the trainers will help to identify these cases.

The second physical activity measurement will be quite soon (10 weeks after the first day at the health resort) after the residential stay and has been discussed at depth within the study group. Follow Up1 will only consist of physical activity measurements and the assessment of psychological mediators. The reason for this is that we are interested in whether short-term changes in physical activity patterns are possible within a short period of time. This information will also be interesting for the 12-months follow-up, because, compared to Follow Up1, the weekly amount of health-enhancing physical activity might have declined, but it should still have increased compared to the baseline level.

In summary, linking the health sector with the sports sector enables the access to community-based structures to increase the weekly amount of health-enhancing physical activity.

